## Abstract

**Introduction:**

Interventions to promote health and well-being based on the construction of psychological resources can positively impact the daily life of users and foster human flourishing. Nowadays, mobile health represents a safe way to support health research and implement evidence-based psychological interventions. The present study aims to evaluate the effectiveness of a mobile app-based intervention program (OneUS) designed to cultivate positive emotions and positive thinking to improve overall well-being.

**Methods:**

The study is designed as a randomized controlled trial. Two hundred participants will be randomly assigned to either a mobile health intervention condition (OneUS App) or an active control condition. The intervention consists of a program to cultivate positive emotions and positive thoughts. The active control intervention will comprise a set of mental imagery exercises and daily routine recording. The primary outcome comprises optimal well-being assessed using the multidimensional PERMA-Profiler scale. The sample will include adult people from the general population, who will be assessed at 8 time points: baseline (t1), intervention (t2, t3, t4, t5, t6) post-intervention (t7) and 3-month follow-up (t8).

**Discussion:**

Mobile apps seem to be promising tools to promote health and well-being. This study will evaluate the effectiveness of a mobile app (OneUS) aiming to cultivate positive emotions and positive thinking to improve well-being. The main strength of this study is the development of an evidence-based mobile health app, based on intentional mental training, to promote well-being. The limitations of this study relate to potential participant drop-out and the non-generalizability of the results to clinical populations.

**Clinical trial registration:**

https://ensaiosclinicos.gov.br/rg/RBR-43hpwqk, Identifier RBR-43hpwqk.

## Introduction

Well-being is a multidimensional construct that includes a hedonic and an eudaimonic component (Dahl et al., 2020). Hedonic well-being, often associated with feeling good, refers to experiencing more positive and less negative emotions, and higher levels of life satisfaction (Diener, 1984; Diener et al., 2017); whereas eudaimonic well-being, often associated with functioning well, includes self-acceptance, positive relationships, autonomy, mastery of the environment, purpose in life, and personal growth (Ryff, 1989; Martela and Sheldon, 2019). According to Seligman (2011), well-being is composed of five domains independently measured, represented in the acronym PERMA: Positive emotions (subjective measures of happiness and life satisfaction), Engagement (active involvement in activities), Relationship (positive connections with family, friends and colleagues), Meaning (the belief in something bigger than oneself) and, Accomplishment (motivation to fulfill personal goals and the satisfaction when those goals are achieved) (Butler and Kern, 2016). The combination of these domains contributes to fostering human flourishing and optimal life functioning at individual and collective levels (Seligman, 2011).

Research suggests that interventions to promote well-being that are focused on happiness, pleasure, and optimal psychological functioning are the most effective (Boiler et al., 2013; Weiss et al., 2016; Hendriks et al., 2020). A recent meta-analysis of 393 studies on different types of psychological interventions showed that interventions focused on building positive psychological resources (fortitude, gratitude, compassion, optimism) tend to have higher effect size estimates than those focused on reducing and controlling negative mental states (e.g., dysfunctional thoughts or psychopathological symptoms) (van Agteren et al., 2021). According to research, positive emotions and positive thinking help build personal or social resources that predict, over a lifetime, improvements in well-being ranging from increased hedonic experiences to increased psychological growth and life meaning (Kiken and Fredrickson, 2017; Coffey et al., 2022).

Positive emotions are multifaceted response tendencies that encompass physiological, subjective, cognitive, and behavioral aspects. They serve to broaden thoughts and actions in the present moment, leading to the development of long-lasting personal resources (Fredrickson, 2001). Positive emotions such as gratitude, hope, pride, love, and serenity can occur frequently in everyday life. Gratitude arises when individuals recognize someone or something as a source of good fortune. Hope emerges during challenging times when people aspire for the best outcomes. Pride arises when individuals attribute the fulfillment of their goals to their efforts. Love appears from meaningful interpersonal connections or relationships. Serenity is experienced when people perceive their circumstances as satisfactory, appreciated, or aligned with their values (Fredrickson, 2013). The experience of these positive emotions enriches well-being, and fosters greater social integration and satisfaction across various aspects of life, happiness, and resilience in the face of adversity (Fredrickson and Joiner, 2002; Silton et al., 2020).

On the other hand, positive thinking refers to a cognitive process that involves creating hopeful mental images, fostering optimistic beliefs, seeking advantageous problem-solving strategies, and cultivating an overall positive perspective on life (Bekhet and Zauszniewski, 2013). To develop positive thoughts, specific skills are employed, including transforming negative thoughts into positive ones, emphasizing the positive aspects of a situation, interrupting pessimistic thinking patterns, generating optimistic thoughts about problems, and devising methods to challenge negative thoughts. Positive thinking training emerges as a significant factor in enhancing well-being: empowering individuals to exert control over their life circumstances through positive appraisals of events and cultivating a pervasive optimistic perspective regarding their future, as well as the meaning and significance of life (Safari and Akbari, 2018; Chui and Chan, 2020).

Although the effectiveness of interventions to improve well-being has been demonstrated in controlled face-to-face settings, some difficulties and challenges may arise during the intervention process, such as non-attendance of participants, staff attrition, staff shortages, high costs, or laborious administration of assessment techniques and instruments (Griffiths et al., 2006). With the advent of new technologies and online tools, however, web-based intervention programs have emerged as a potential solution to these issues, offering advantages such as ease of access, rapid administration, and the ability for participants to engage in self-directed participation without the need for constant supervision (Marciniak et al., 2020; Szinay et al., 2020).

Mobile health (mHealth) is an example of the safe and cost-effective use of information and communication technologies (ICTs). The mHealth encompasses the use of mobile devices, such as cell phones, personal digital assistants, and other wireless devices, to support healthcare practices in various fields including medicine, psychology, and public health (World Health Organization, 2011). mHealth has contributed to increasing universal health coverage by providing timely information, decreasing overload on services, and enabling synchronization of care with daily lives of the users (Free et al., 2013; Marzano et al., 2015). To take advantage of these benefits, there are increasing efforts to design psychological interventions based on mobile applications to generate a positive impact on well-being and health (see Lorca-Cabrera et al., 2020 for a review): these interventions provide an accessible means to incorporate positive practices into existing routines and facilitate the adoption of new healthy habits (Diefenbach, 2018). Educational activities, along with techniques such as mindfulness, goal setting, future visualization, positive thought journaling, and mental imagery, might contribute to the success of technology-based well-being interventions (Howells et al., 2014; Riva et al., 2016; Eisenstadt et al., 2021).

The rapid advance of digital innovation has led to the availability of more than 350,000 health apps in major mobile app stores around the world. Among them, 47% are dedicated to well-being, according to data from IQVIA Institute for Human Data Science (2021). Despite the abundance of options, most apps lack adequate evaluations to determine their effectiveness in promoting and improving well-being (Donker et al., 2013). Although a recent meta-analysis suggests that health apps offer promising benefits in improving well-being, the overall effect size remains small based on pooled analysis (g = 0.17, 95% CI 0.05 to 0.29, *p* = 0.004) (Eisenstadt et al., 2021), and there is limited information on the long-term sustainability of these benefits beyond the intervention period (Boiler and Abello, 2014). Mobile apps are valuable tools that can provide quick and accessible benefits to many people; however, it is crucial that these apps are evidence-based to ensure their effectiveness and mitigate any potential adverse effects caused by their use.

Thus, a smartphone app named OneUS has been developed to support people in cultivating well-being through positive thinking and positive emotions (gratitude, hope, pride, love, and serenity). The app utilizes intentional mental training techniques and includes a library of psychoeducational content and guided exercises. By increasing awareness and teaching skills to cultivate positive emotions and train positive thinking in daily lives (Bekhet and Zauszniewski, 2013; Fredrickson, 2013), OneUs aims to enhance overall well-being. The app offers content in various formats, such as videos, audio, and text, which are enabled weekly after the completion of the visualization and activities. The app sends notifications and reminder messages to motivate users to continue the training, which will increase adherence rates.

This study aims to evaluate the effectiveness of a mobile app-based positive psychology intervention to improve people’s well-being through the daily practice of activities aimed at positive emotions and positive thinking. The study will test the hypothesis that using the OneUS mobile application for the daily practice of positive emotions and positive thinking enhances well-being and reduces psychological distress in a sample of adults from the general Brazilian population.

## Methods

### Study design

The protocol for this study received approval from the Research Ethics Committee of the Health Institute of the Federal University of Pará, Belém, Brazil (code number: CAAE: 58610822.1.0000.0018). The study was designed as a two-arm cluster-randomized controlled trial comparing an intervention condition and an active control condition. The stages of this study will include baseline assessment, implementation of the intervention, and weekly evaluation at seven measurement points. The stages of the study are shown in Figure 1. This study will be conducted in accordance with the Consolidated Standards of Reporting Trials (CONSORT) statement (Boutron et al., 2017) and the Consolidated Standards of Reporting Trials of Electronic and Mobile Health applications and online Telehealth (CONSORT-EHEALTH) checklist (Eysenbach and CONSORT-EHEALTH Group, 2011).

**Figure 1 fig1:**
[figure not shown]
Stages of the study based on CONSORT diagram.

## Participants

### Sample size

This study will be conducted in Brazil. Participants will be recruited through advertising messages on social networks. In these messages, potential participants will find a link to a Google form to make an initial registration and provide their email addresses. The study aims to include 200 eligible participants, 100 per condition (active control and experimental). The General Linear Mixed Model Power and Sample Size 3.0 calculator (GLIMMPSE 3.0) (Kreidler et al., 2013) was used to determine the required sample size considering the study design, fixed predictors of conditions (active control and experimental), Time (t1, t2, t3, t4, t5, t6, t7, and t8), and Conditions x Time interaction effects. Using Hotelling Lawley Trace with power 0.8 and type I rate 0.05, total sample size was calculated as 76; however, 100 participants per condition will be selected to account for potential dropouts.

### Eligibility criteria

Participants will be selected through a step-by-step process that involves meeting certain eligibility criteria. To be eligible for inclusion in the study, participants must be adults (18 years or older), have access to the internet and a mobile device with an Android operating system, be a resident of Brazil, provide consent through an online form, agree to use the app, and complete the questionnaires. Individuals will be excluded if they have mental health problems. The General Health Questionnaire-12 (GHQ-12) will be utilized in this study to assess the risk of common mental disorders (CMD). It consists of 12 items and employs a Likert scale ranging from 1 to 4. A score of 1 indicates “More than usual,” while a score of 4 indicates “Much less than usual.” Each item on the questionnaire is scored as either absent (0) or present (1). Responses of 1 or 2 are considered absent (0), while responses of 3 or 4 are considered present (1). Participants who score positive for 3 or more items on the GHQ-12 will be classified as cases of CMD (Gouveia et al., 2003), and will be excluded from the study. In addition to the GHQ-12, two additional questions will be included to identify participants who have a diagnosis of psychological disorder or are currently undergoing psychological treatment for any mental health issues. The questions are as follows: “Do you have a diagnosis of a psychological disorder?” and “Are you currently receiving psychological treatment for any mental health issues?” Individuals who respond “Yes” to either of these questions will be excluded from the study.

### Recruitment

Potentially eligible participants who have pre-registered will be contacted by e-mail. In this message, they will be informed about the general aspects (i.e., rationale for the study, responsible institutions, benefits, procedures) and objectives of the study. In addition, they will be sent a link to access the App store to download the OneUS app for free. The recruitment of participants involves a self-selection process through the app. During this process, individuals will be required to respond to a series of questions that will be used to evaluate the selection criteria explained above. Based on their answers, the application will then determine whether to include or exclude them from the study. Noteworthy, the application incorporates a security mechanism designed to prevent access by bots and mitigate the risk of Distributed Denial of Service (DDoS) attacks. Upon installation, participants will be required to complete a pre-registration process, accept the terms, and verify their profiles using a code sent *via* email or text message. This procedure ensures that only human participants gain access to the application, safeguarding and guaranteeing the security of their personal data and the progress achieved in the mobile application.

## Procedures

### Randomization and blinding

Participants will be randomly assigned to either the intervention condition or the active control condition using R software (Version 4.0.5) and the R package randomizr. The allocation ratio will be 1:1. The randomizr function, applied by a blinded research assistant, will randomly assign a value of 0 or 1 to each participant, representing their experimental condition (0 = Experimental; 1 = Active Control). Although participants and evaluators will not be blinded to the intervention during the study, the data analysts will be blinded. Participants may be able to determine which condition they are in due to the educational and informative content they receive about positive emotions and positive thinking.

### Interventions

OneUs is an application developed by the authors in collaboration with Educa Tecnologia, a Brazilian company that provided computer programming services. The App has two sub-applications: an intervention app and a control app. Once potential participants are selected, they will be randomly assigned to one of these sub-applications.

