### Active control condition

The comparator will be an active control condition. Participants in this condition will be trained in mental imagery exercises in normal everyday life situations. This condition will be considered an active control because the participants will perform mental imagery of neutral events and emotion monitoring. The app design for this condition will have the same structure as the experimental condition and will include a user profile, menu, assessment measures, and notifications.

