## Outcome measures

The outcome measures will be completed at 8 time points: baseline (t1), intervention (t2, t3, t4, t5, t6) post-intervention (t7), and 3-month follow-up (t8), following the recommended timeline outlined in the SPIRIT 2013 statement (refer to Table 2). The SPIRIT 2013 statement serves as a checklist for clinical trial protocols, offering guidelines on the essential content and a standardized diagram of activities, interventions, and measures (Chan et al., 2013).

**Table 2 tab2:** Schematic diagram for timeline participant.

	Enrolment	Baseline	Intervention					Close-out	Follow-up
TIMEPOINT	*0*	*t1*	Week 1 (t2)	Week 2 (t3)	Week 3 (t4)	Week 4 (t5)	Week 5 (t6)	*t_7_*	*t8*
Enrolment:									
Eligibility screen	X								
Informed consent	X								
Allocation	X								
Interventions:									
Training and daily practice of positive emotions and positive thinking									
Active control									
Assessments:									
Socio-demographic characteristics	X								
Well-being		X	X	X	X	X	X	X	X
Optimism		X	X	X	X	X	X	X	X
Hope		X	X	X	X	X	X	X	X
Subjective Happiness		X	X	X	X	X	X	X	X
Stress		X	X	X	X	X	X	X	X

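### Table 2 places allocation before the self-reported t1 baseline in an open-label trial, so t1 could be influenced by knowledge of the arm

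*Protocol article*

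**What the plan says.** Three parts of the protocol article bear on the order of events.

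- **Interventions:** after describing the two sub-applications, the section states "Once potential participants are selected, they will be randomly assigned to one of these sub-applications". No baseline step is named between selection and assignment. Under Recruitment, selection is the eligibility screen inside the app.
- **Outcome measures, Table 2** ("Schematic diagram for timeline participant"): the Allocation row has a single mark, in the Enrolment column (timepoint 0), alongside eligibility screening and consent. Well-being, optimism, hope, happiness and stress have no mark there; each starts in the next column, Baseline (t1). Socio-demographic data are marked at Enrolment.
- **Active control condition:** the control app "will have the same structure as the experimental condition and will include a user profile, menu, assessment measures, and notifications".

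On blinding, Randomization and blinding says "Although participants and evaluators will not be blinded to the intervention during the study, the data analysts will be blinded". It adds: "Participants may be able to determine which condition they are in due to the educational and informative content they receive".

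Data analysis methods fits linear mixed models with Condition, Time and their interaction, and t1 is one of the eight levels of Time.

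**The concern.** All outcomes are self-report scales completed in the app, so they are open to expectation or disappointment once a participant knows or guesses the arm. Randomisation guarantees equal expected baseline means only for a baseline fixed before allocation can affect it. If t1 comes after allocation and participants can recognise their arm by then, that protection is lost for the value against which every later change is measured. A shift confined to t1 in one arm is itself a Condition x Time effect, even if all later means are equal.

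There is a second consequence that needs no assumption about blinding. A person who is allocated and leaves before completing t1 is a randomised participant with no outcome data at all. If t1 came first, the same person would be a registrant who was never randomised.

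**Working it through.** **Step 1: the order of events.** Set side by side, the sources give:

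| Source | What it shows about the order |
|---|---|
| Table 2 | Allocation at timepoint 0; all five scales first at t1 |
| Interventions | Sub-app assigned on selection; no baseline step named before it |
| Active control condition | Assessment measures listed as part of the allocated sub-app |
| Study design | Baseline assessment named first among the stages, but not placed relative to randomisation |
| Figure 1 | Not available here |

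Table 2 puts allocation before t1, the Interventions text is consistent with that, and no available text puts t1 first.

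**Step 2: could the arm be known at t1?** The stated route to recognising the arm is the educational content. The experimental app has an introductory session on the advantages of positive emotions and positive thinking. It is described before the first week, and Table 1 assigns it to no week. Week 1 is t2, so the session may fall in the same window as t1. Nothing says t1 must be submitted before it opens, and nothing says the reverse.

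**Step 3: what a shift would do.** Let δ be the difference between arms in mean outcome at a later time, and b the difference at t1 caused by knowledge of the arm, both in SD units and as experimental minus control. Then

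expected change-from-t1 contrast = δ − b.

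The bias has size |b|. If t1 is raised in the experimental arm (b > 0), the app's effect is understated; if b < 0, it is overstated.

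**Step 4: illustration of size.** From the article: 100 per arm and type I error 0.05, taken here as two-sided. Assumed: b; correlation ρ between t1 and the later value; equal variances; complete data; and a normal test of one change contrast rather than the full interaction test.

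- SD of change = √(2(1 − ρ)): 1.000 for ρ = 0.5 and 0.775 for ρ = 0.7.
- SE of the contrast = SD × √(2/100): 0.141 and 0.110.
- Error when δ = 0: Φ(−1.96 + b/SE) + Φ(−1.96 − b/SE).

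| Assumed b (SD) | ρ = 0.5 | ρ = 0.7 |
|---|---|---|
| 0 | 0.050 | 0.050 |
| 0.05 | 0.064 | 0.074 |
| 0.10 | 0.109 | 0.150 |

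The plan gives no figure of its own for this question. Its calculated total of 76 cannot be reproduced, because no effect, SD or correlation is stated; the point does not depend on it.

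**The case against.** The strongest reply is that being allocated is not the same as knowing the arm. No text says participants are told their arm at allocation. The control app shares the structure of the experimental one, and Table 2 gives t1 its own column ahead of the intervention weeks. If no content opens before t1, participants may be unable to tell the arms apart when they answer. This stands, and it limits the point to a risk.

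It can also be said that Table 2 is coarse, that the Interventions wording does not claim immediacy, that an assistant runs the allocation in R rather than the eligibility screen triggering it, and that screen order belongs in the full protocol. This stands only in part. The article does not merely omit the order: Table 2 states one, and nothing available states another. If the app in fact takes t1 first, Table 2 and the Interventions text misdescribe it and still need correcting.

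Two stronger readings are tempting and are not supported:

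- **That t1 is contaminated.** This would need evidence that arm-revealing content is seen before t1, which the article does not give.
- **That the bias is a large share of the effect sought.** An assumed shift of 0.10 SD is 59% of the pooled g = 0.17 in the Introduction (0.10/0.17). But that g is a background estimate, and Sample size states no design effect. Back-solving 38 per arm as a simple comparison of two means gives d of about 0.50 to 0.64, for final scores or for change scores with assumed correlations of 0.5 to 0.7. Against that, the same shift is 16% to 20%. Neither ratio describes this trial, because the 0.10 is itself an assumption.

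**Conclusion.** The point holds as a risk to the reference value of the Condition x Time test, created by the stated order of allocation and t1 in an open-label, self-report trial. It is not a demonstrated or quantified bias. What is certain is the form: a differential t1 shift of b SD biases the change-from-t1 contrast by b SD in size. The direction and size of b are unknown. The error rates of about 0.06 to 0.15 rest wholly on assumed shifts of 0.05 to 0.10 SD and assumed correlations of 0.5 to 0.7. Under the order in Table 2, loss between allocation and t1 leaves randomised participants with no data; the number cannot be predicted from the article. The change is worth making before enrolment starts because it removes the question at almost no cost.

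**What to change.** Collect consent, eligibility and the full t1 battery in the part of the app common to both arms. Make or release the allocation, and open the sub-app, only after t1 is submitted. Move the Allocation mark in Table 2 to after t1, and reword the Interventions sentence so that assignment follows selection and completion of t1. If the app already works this way, only the table and the wording need changing.

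The cost is a change of screen order, one table cell and one sentence. An assistant already runs the allocation in R, so holding it until t1 arrives is feasible. Neither the sample size nor the analysis model changes. The downside is that a few registrants will stop before randomisation, which does not harm validity.
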